### Primary and secondary outcomes

This controlled trial will use a wide range of clinical and patient-reported outcomes measures to assess the cost-effectiveness of this intervention. The outcomes are set with reference to the *Medical Research Council framework for evaluating complex intervention* (31) and on the *American Diabetes Association's Standards of Medical Care in Diabetes 2021* for diabetes research (32).

We have two primary outcomes in this trial. Glycated hemoglobin (HbA1c) will be measured by self-test kit (Polymer Technology Systems Inc., Whitestown USA), and fasting blood sample for plasma glucose will be measured by blood glucose monitor (ForaCare Inc, Moorpark USA).

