### Data analysis

We will adopt both qualitative and qualitative approaches to evaluate the impact of lay health worker intervention in pre-diabetes management in this trial.

A quantitative methodology will be adopted to evaluate the intervention effectiveness by performing group-wise comparison of the primary and secondary outcomes in this study. A CONSORT flowchart will be adopted to present the progress and of this trial. We will adopt an intention-to-treat approach in conducting the analysis, with sensitivity analysis to be done with non-ignorable missing data. Descriptive statistics will be produced for primary and secondary outcomes depending on their measurement scale and data distribution to allow meaningful interpretation. Histogram of the data distribution will be plotted to examine whether the data is parametric, or non-parametric. We will produce mean and standard deviation for parametric data, and use median and inter-quarter range for non-parametric data. Number and percentage will be quoted for ordinal and nominal data. Standardized mean differences of each variable will be produced to evaluate the balance in control and intervention groups, with a value larger than 0.1 indicating an imbalance between groups.

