In order to compare the effectiveness of intervention between control and the intervention group at the exit assessment of intervention (6^th^ month), we will use repeated-measures Analysis of Variance (ANOVA) for parametric outcomes. We will consider the measures of data at baseline (0^th^ month) and covariates that are imbalanced in control and intervention groups when conducting ANOVA, and the effect size will be estimated by calculating the Cohen's *d* value. For non-parametric variables, the Friedman test will be done, and Kendall's W value will be produced for effect size estimation. For ordinal data, we will use Generalized Estimating Equations to compare groups at each follow-up (0^th^ month, 6^th^ month, and 12^th^ month), allocation group (intervention and wait-list control), time by group interaction, covariates that are imbalance between groups, and important socio-economic variables including sex, age, and education level. We will use an identify link function given a normal distribution of the captioned outcome. Also, Kaplan-Meier curves will be drawn to capture the comparison of diabetes-free survival in the intervention and control group. The level of significance is set at 5% m and *post-hoc* adjustment will be applied for multiple comparisons. Multiple imputations will be used whenever appropriate for missing data. In this analysis, all statistical analyses will be conducted using R and RStudio, and the Cohen's *d* value will be estimated using G^*^Power.

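### The Friedman test named for non-normal outcomes compares time points within participants, not randomised arms, so a skewed HbA1c would have no between-arm test

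*Protocol article*

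**What the plan says.** The Data analysis section of the protocol article describes the quantitative evaluation as "performing group-wise comparison of the primary and secondary outcomes in this study". It states the aim as to "compare the effectiveness of intervention between control and the intervention group at the exit assessment of intervention", that is, month 6. Methods are then assigned by type of outcome:

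- Parametric: "we will use repeated-measures Analysis of Variance (ANOVA) for parametric outcomes", taking account of baseline and imbalanced covariates, with Cohen's d.
- Non-parametric: "For non-parametric variables, the Friedman test will be done", with Kendall's W as the effect size.
- Ordinal: "For ordinal data, we will use Generalized Estimating Equations to compare groups at each follow-up", in a model with allocation group, a time-by-group interaction and covariates.

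The only stated means of telling the first two types apart is this: "Histogram of the data distribution will be plotted to examine whether the data is parametric, or non-parametric". Kaplan-Meier curves are also planned, for diabetes-free survival.

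Under Primary and secondary outcomes the article says "We have two primary outcomes in this trial": HbA1c and fasting glucose, both continuous. Table 1 lists HbA1c alone as primary.

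**The concern.** The Friedman test needs related measurements within each block. Here the block is the participant, and the two arms are different people (111 and 111), so arm cannot be the factor under test. The test can compare only time points, either pooled over arms or separately in each arm.

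- **Pooled**, it rejects when both arms improve equally and can miss a real difference between arms.
- **By arm**, it leads to the fallacy of reading significance in one arm and not in the other as a treatment effect.

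Kendall's W measures how consistently participants rank the time points. It is not a treatment effect either.

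A common improvement is plausible here. The Control group selection section gives controls health information, weight-control management and dietary education during the wait. The same rule also reaches the continuous secondary outcomes, such as waist circumference, body fat and food-record values.

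**Working it through.** **1. The statistic with two time points.** With n participants, k times and rank sums R_j, the Friedman statistic is

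χ² = 12/(n·k·(k+1)) · ΣR_j² − 3n(k+1).

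For k = 2, let n₊ participants rise, n₋ fall, and n = n₊ + n₋. Then R₁ + R₂ = 3n and R₁ − R₂ = n₋ − n₊, so ΣR_j² = [9n² + (n₊ − n₋)²]/2. Hence

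χ² = (2/n)·[9n² + (n₊ − n₋)²]/2 − 9n = (n₊ − n₋)²/n.

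This is the sign test. Computed both ways on one data set, the p-value was 0.294 each time. Kendall's W = χ²/(n(k−1)) = ((n₊ − n₋)/n)². Arm appears in neither expression.

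**2. Inputs.**
- From the protocol (Sample size calculation): 111 per arm, 20% dropout, SD 1.5, difference 0.5.
- Completers: 111 × 0.8 = 88.8, taken as 89 per arm and n = 178 pooled.
- Planned difference: 0.5/1.5 = 0.333 SD.
- Assumed, not in the protocol: bivariate normal values, correlation ρ = 0.6 between baseline and month 6 (range 0.4 to 0.8 below), and the common falls.

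**3. Rejection rule at 5% (critical χ² 3.84).** Pooled: 26²/178 = 3.80 and 28²/178 = 4.40, so |n₊ − n₋| must be at least 28. Per arm: 17²/89 = 3.25 and 19²/89 = 4.06, so at least 19.

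**4. No treatment effect, both arms fall by s SD.** The SD of change is √(2(1 − 0.6)) = 0.894. The probability that a participant falls is Φ(s/0.894). The binomial distribution then gives:

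| Common fall s | P(fall) | Pooled Friedman rejects |
|---|---|---|
| 0 | 0.500 | 4% |
| 0.1 | 0.545 | 20% |
| 0.2 | 0.589 | 64% |
| 0.3 | 0.631 | 94% |

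Simulation with 5000 trials per scenario gives 4.5%, 19.9%, 63.6% and 93.5%. Run by arm at s = 0.2, each arm rejects with probability 0.407, so significance in the intervention arm only occurs in 0.407 × 0.593 = 24% of null trials.

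**5. True difference of 0.333 SD.**
- Split evenly (controls +0.167, intervention −0.167): pooled Friedman rejects in 4%.
- Controls flat, intervention −0.333: P(fall) is 0.500 and 0.645, and pooled Friedman rejects in 47%.
- Mann-Whitney on change: about 68% power at this difference, and 4.6% rejection under the 0.2 SD null.

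**6. Sensitivity to the assumed correlation.**

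| ρ | Pooled Friedman, null with both arms −0.2 SD | Pooled Friedman, controls flat | Mann-Whitney power |
|---|---|---|---|
| 0.4 | 47% | 33% | about 50% |
| 0.6 | 64% | 47% | about 68% |
| 0.8 | 91% | 75% | about 92% |

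**7. Skewed data, the case in which the rule would apply.** Assumptions: lognormal outcome with log-scale SD 0.5, scaled to SD 1.5; log-scale correlation 0.7; 89 per arm; 4000 runs.

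| Control change | Intervention change | Pooled Friedman | Friedman in intervention arm | Mann-Whitney on change |
|---|---|---|---|---|
| −0.5 | −0.5 | 100% | 98.5% | 5.0% |
| +0.25 | −0.25 | 3.4% | 57.9% | 89.7% |
| 0 | −0.5 | 79.2% | 98.6% | 89.2% |

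The Friedman result follows the time trend. The between-arm test follows the difference between arms.

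**The case against.** The strongest reply is that this branch is conditional. The first-named analysis is a repeated-measures ANOVA that takes account of baseline, and the sample size rests on means. Nothing in the protocol says that HbA1c will be classed as non-parametric, and if only one primary outcome is so classed, the other keeps a between-arm test. That is true and limits the consequence. It does not make the rule valid where it applies, and Table 1 names HbA1c as the only primary outcome.

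The GEE model has the right terms, and its identity link with a normal distribution would suit a continuous outcome, so the ordinal label may be a slip. As written, though, it covers ordinal data only. The Kaplan-Meier comparison concerns another endpoint.

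The histogram sentence stands among the descriptive statistics. That it also selects the test is the natural reading, but it is not stated. Data-dependent selection is therefore a secondary point.

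The article allows for more than two assessments and lists month 12 for the GEE. With three times the test is no longer a sign test and the percentages above would not apply. It would still have no arm term, and controls are offered the intervention after month 6.

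Finally, the 4% figure is the extreme case, with controls worsening as much as the intervention arm improves. With flat controls the figure is 47%. The percentages illustrate the problem and do not predict what this trial will show.

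**Conclusion.** The concern holds. For a continuous outcome classed as non-parametric, the protocol names a test that cannot make the between-arm comparison it sets out to make. This is a wrong method stated in the text, not a detail left to an analysis plan. The conclusion follows from the definition of the statistic and needs no assumption about the data.

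The size does depend on assumptions. Over correlations of 0.4 to 0.8, a shared fall of 0.2 SD with no treatment effect produces pooled rejection in about 47% to 91% of trials, against a nominal 5%. A real difference of 0.33 SD is detected in anything from about 4% (centred on zero) to 33% to 75% (controls flat). The consequence arises only if an outcome is classed as non-parametric. Because that can happen to a primary outcome, the rule must be corrected before analysis.

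**What to change.** Delete the Friedman test and Kendall's W. For all continuous outcomes, prespecify one between-arm analysis that does not depend on the shape of a histogram: ANCOVA of the month-6 value adjusted for baseline, on the log scale or with robust or bootstrap standard errors if residuals are skewed. Add a between-arm non-parametric sensitivity analysis: rank ANCOVA, or Wilcoxon-Mann-Whitney on change from baseline with a Hodges-Lehmann estimate and confidence interval.

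The minimum repair is to replace Friedman with one of these between-arm rank methods. Using a single ANCOVA throughout goes further, because it also replaces the ANOVA route, but it removes the data-dependent choice of test. The cost is analysis wording only. Baseline and month-6 values are already collected.

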## Methods and analysis

### Study design

This randomized controlled trial aims to evaluate the impact of a lay-health worker intervention on the disease management of type II diabetes mellitus (T2DM) among Chinese sub-divided flat residents units in Hong Kong, comparing to the wait-list controls who receive usual care. This trial is a part of a community, diabetes-screening programme which targets families living in sub-divided homes, aiming to provide disease management to the population diagnosed with diabetes or identified with risk to develop diabetes. This lay worker intervention contains five features, including: (1) lay health worker training and support; (2) health professional training, (3) formulation of a targeted care plan for the health and nutritional needs of the families; (4) case management approach; and (5) financial subsidy for lay health workers to sustain the practice. This trial will be reported in accordance with SPIRIT 2013 checklist (22), as enclosed in Supplementary material S1. Figure 1 comprises the workflow of this trial. Table 1 includes the minimal data set for trial registration.

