### Control group selection

This study will have a wait-list control, where the control will receive usual care of health information on diabetes risk management, conventional weight-control management and dietary education during the 6 months waiting period. On completion of the waiting period, the nurse and dietitian will invite the control group's participants for a face-to-face consultation, where the clinical staff and lay health workers will have a chance to identify their service needs and give tailored care plans.

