### Sample size calculation

Two hundred and twenty-two participants are needed (111 for intervention, 111 for control at a 1:1 case to control ratio) to attain 80% power, 95% level of significance and 20% dropout rate in a population with an expected population standard deviation of 1.5, and an allowable difference of 0.01 to detect a change of 0.5% change in HbA1c concentration. We plan to train 70 lay health workers on a 1:4 lay health worker to patient ratio, and assuming a 20% dropout rate.

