We will use a mixed-method approach to conduct the process evaluation on the participants. Quantifiable, routine data will be collected to evaluate the output of this intervention in corresponding to the five components of this intervention as described in Table 2, following with a *t*-test to compare intra-groups estimates to allow meaningful interpretations at the 6^th^ and 10^th^ month. The results from quantitative study part will provide a description for the overall execution of the intervention, which inform the answer for the following research questions: (1) what outputs were delivered to achieve the five components of the interventions; and (2) to which extend did the different stakeholders (study participants, healthcare worker, and lay health workers) complete/ adhere to the intervention? In complimentary to the quantitate research, the qualitative part of the mix-method study will be conducted in parallel. Two rounds of qualitative semi-structured, auto-taped individual interviews will be conducted at 6^th^ months (the completion of wait list control period) and 12^th^ month (project endpoint), to collect feedbacks from different stakeholders involved in this project. Project staffs (*n* = 2), lay health workers (*n* = 10), healthcare professionals participated (*n* = 5), NPO collaborators (*n* = 5) and study participants (*n* = 10) will be invited to participate in this study. Each individual interview will last for 1–1.5 h, with the following research questions to be answered: (1) what are the feedback and major concerns of the participants of the programme; (2) how to address these concerns in the second cycle of intervention?; (3) what are the facilitators and barriers in the programme delivery; and (4) how to enhance the facilitators or mitigate the barriers?, as guided by the *Consolidated Framework for Implementation Research* (37). Detailed interview questions can be found in Supplementary material S5. All the interviews will be conducted by research staff that is not involved in the delivery of this trial to ensure impartiality.

**Table 2 T2:** Outline of the process evaluation: output indicators.

**Component**	**Output**	**Indicators**	**Source of data**
1. Lay health worker training	More trained workers	Number of training sessions conducted	Administrative data
		Number of total lay health workers trained	Administrative data

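### The month-12 group comparison, and any Kaplan-Meier curve running past month 6, compares early with delayed intervention, because the wait-list arm starts treatment after month 6

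*Protocol article*

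**What the plan says.** **Crossover.** Under Control group selection, the wait-list arm has usual care for 6 months. It is then invited to a consultation, "where the clinical staff and lay health workers will have a chance to identify their service needs and give tailored care plans". The Discussion gives access to the intervention for both groups as a reason for the design. The process-evaluation text in Data analysis treats month 6 as the end of the waiting period and month 12 as the end of the project. It asks interviewees "how to address these concerns in the second cycle of intervention", so a second cycle follows month 6.

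**Analyses.** Data analysis places the repeated-measures ANOVA at the month-6 exit assessment. For ordinal data it plans "Generalized Estimating Equations to compare groups at each follow-up (0^th^ month, 6^th^ month, and 12^th^ month), allocation group (intervention and wait-list control"), with a time-by-group interaction. It then adds: "Kaplan-Meier curves will be drawn to capture the comparison of diabetes-free survival in the intervention and control group". No horizon is given for the curves, and no rule for follow-up after controls cross over.

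**Measurement and eligibility.** The Abstract has HbA1c and fasting glucose taken at entry and exit. The data collection section speaks of at least two time points. The criteria under Selection of subjects recruit on risk factors or symptoms and do not exclude existing diabetes. Study design describes the wider screening programme as "aiming to provide disease management to the population diagnosed with diabetes or identified with risk to develop diabetes".

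**The concern.** From month 6 onward no randomised group remains untreated. A comparison by allocation group at month 12, presented as evidence of effectiveness, answers a different question from the trial's own, which is the intervention against usual care. Nothing in the text says that contrasts after month 6 are to be read as early versus delayed.

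A null month-12 result could be reported as no lasting benefit when the delayed arm has simply caught up. A reversed result could be reported as harm when the early arm has lost part of its gain while the delayed arm has just finished treatment. The same applies to a statement on diabetes incidence drawn from curves that run through the crossover. This matters because the Introduction names incidence among the things the trial is meant to evaluate.

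**Working it through.** The plan gives no figure for a 12-month contrast or for diabetes incidence, so there is none to reproduce. The calculations below show the mechanism only.

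**1. Month-12 contrast**

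Input from the document: a 0.5-point HbA1c difference (Sample size calculation), used here only as a convenient scale. Assumptions: the early arm keeps a fraction r of its month-6 effect at month 12, and the delayed arm gains a fraction f of that effect between months 6 and 12. Positive values favour the early arm.

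- Contrast obtained: 0.5 × (r − f)
- Contrast against controls who stay untreated: 0.5 × r

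| r | f | Obtained | Against untreated controls |
|---|---|---|---|
| 1 | 0 | 0.5 | 0.5 |
| 1 | 0.5 | 0.25 | 0.5 |
| 1 | 1 | 0 | 0.5 |
| 0.5 | 0.5 | 0 | 0.25 |
| 0.5 | 1 | −0.25 | 0.25 |

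The two columns agree only if f = 0, that is, if the intervention does nothing for the delayed arm. The gap is 0.5 × f, and the sign of the obtained contrast depends on whether r or f is larger.

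**2. Kaplan-Meier curves continued to month 12**

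Assumptions: a cumulative hazard λ per 6 months without treatment and an on-treatment hazard ratio h of 0.5 or 0.7. After the early arm's treatment ends, its effect either persists or stops.

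- Delayed arm, months 0–12: λ(1 + h)
- Early arm: 2λh if the effect persists, λ(h + 1) if it stops
- Never-treated controls: 2λ

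| h | Early-arm effect after month 6 | Early ÷ delayed | Early ÷ never treated |
|---|---|---|---|
| 0.5 | persists | 1.0/1.5 = 0.67 | 1.0/2 = 0.50 |
| 0.5 | stops | 1.5/1.5 = 1.00 | 1.5/2 = 0.75 |
| 0.7 | persists | 1.4/1.7 = 0.82 | 1.4/2 = 0.70 |
| 0.7 | stops | 1.7/1.7 = 1.00 | 1.7/2 = 0.85 |

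λ cancels, so the ratios do not depend on the unknown incidence. Over months 0–6 alone the ratio is λh ÷ λ = h, the true value.

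**3. Kaplan-Meier curves stopped at month 6**

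There is then no crossover problem. However, glycaemia is known only at scheduled assessments, here entry and month 6. Onset is known only to lie between the two, and the curve has essentially one step. It carries the same information as the proportion with new diabetes at month 6. That proportion also needs a denominator of people without diabetes at entry, which the listed criteria do not secure.

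**4. What is unaffected**

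The ANOVA is set at month 6, inside the controlled period. The GEE compares groups at each follow-up and includes the time-by-group interaction, so its month-6 contrast is estimated separately from month 12.

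**The case against.** **The effectiveness comparison is at month 6.** This stands. A reader might infer that the main HbA1c result is diluted, or loses power, through averaging over months 0, 6 and 12. The document does not support that. The three-visit GEE is written for ordinal data, and its interaction keeps month 6 separate. The identity link and normal distribution mentioned next leave its scope unclear, but nothing says HbA1c enters it.

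**The Kaplan-Meier horizon may be fixed elsewhere.** An article condenses, and horizon and censoring could sit in the full protocol or analysis plan. This stands in part. The horizon is unstated, not set at 12 months, so the crossover problem for the curves is conditional. The text also plans only to draw curves and names no log-rank test or hazard ratio. They are nevertheless meant to compare the groups, and a month-6 horizon leaves a one-step curve.

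**Bias toward zero.** A reader might infer simple dilution. The first table shows that the contrast can also change sign.

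**People with diabetes at entry.** A reader might infer from the Study design sentence that the trial enrols them. That sentence describes the wider programme. The document shows only that no listed criterion excludes them, and restricting the risk set at analysis is routine.

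**A changed intervention in the second cycle.** The interview question asks how concerns might be addressed. It does not commit to a revision.

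None of this gives the month-12 group contrast an intervention-versus-control meaning.

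**Conclusion.** The point holds in limited form. The planned month-12 GEE contrast between allocation groups compares early with delayed intervention, and so would any Kaplan-Meier curve continued past month 6. Neither estimates intervention versus usual care.

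On the illustrative 0.5-point scale the month-12 contrast is 0 if both arms end with the full effect. It is +0.25 if the delayed arm gains half while the early arm keeps all, and −0.25 in the opposite case. A true hazard ratio of 0.5 would appear over 12 months as 0.67 or 1.00, and one of 0.7 as 0.82 or 1.00. These figures rest on assumed persistence, assumed gain and a constant untreated hazard. They show the mechanism and do not predict the trial's results.

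The month-6 comparisons stand. What needs correcting is the labelling of the 12-month results and the method for diabetes incidence. The visit schedule is taken from the text, since the workflow figure was not available.

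**What to change.** 1. State in Data analysis that randomised between-arm inference uses months 0 and 6 only, including in the GEE.
2. Report month-12 results either as early versus delayed intervention or as within-arm data: durability in the early arm, and response to treatment in the delayed arm.
3. Replace the Kaplan-Meier curves with the proportion newly meeting the trial's diabetes definition at month 6, among participants without diabetes at baseline, as a risk difference with 95% CI.

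The cost is analysis wording only, with no change to visits or sample size. The 12-month results lose their intervention-versus-control label.

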Alongside the case management duties, lay health workers will continuously assess the physical, mental, and nutritional health status of the participants through patient-reported outcomes. Lay health workers will maintain a close working relationship with the nurse and dietitian. Following each of the telephone follow-up, the lay health workers will participate in a group-based case de-briefing session where they can discuss the difficulties they encountered during the follow-up, and learn from each other's for better consultation skills. Lay health worker will review case progress with nurse/dietitian once every 2–4 weeks, and will discuss the motivators and barriers for the participants' behavioral changes to guide necessary amendments in the care plan. The participants are, therefore, under the co-management of the clinical professional (nurse or dietitian) and the lay health workers. For there is any undesirable outcome identified during the follow-up, the lay health workers will refer the participants for immediate intervention by the nurse and dietitians' management.

Lastly, financial subsidy will be provided to lay health workers to ensure the sustainability of their practice, and as a reward to honor their time spent on providing services to the participants.

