	Lay health workers being more confident to lead intervention	Knowledge, attitude and behavior in leading an intervention	Self-administered survey before and after training
2. Health professional training	More health professionals are equipped with the necessary knowledge to co-work with lay health workers	Number of training sessions conducted	Administrative data
		Number of health professionals trained	Administrative data
		Knowledge, attitude and confidence in collaborating with lay health workers	Self-administered survey before and after training
3. Formulation of targeted care plans	Tailored care plan built for participants	Number of health need assessments conducted	Administrative data
		Number of targeted care plans formed	Clinical and service record
		Completion rate of designed health goals	Clinical and service record
4. Case management	Close and tailored case management for participants	Number of families followed-up by lay health workers	Administrative data
		Number of lay health workers follow-up conducted	Administrative data
		Number of biweekly reviews meeting conducted between lay health workers and nurse/ dietitian	Administrative data
		Number of families followed-up by the same lay health workers	Administrative data
5. Financial subsidy for lay health workers	More lay health workers recruited	Number of lay health workers recruited	Administrative data
	Sustainable service model	Proportion of lay health workers that finished the 6-months follow-up	Administrative data

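### The second quantitative process readout is set at month 10, two months before the wait-list arm's six-month cycle ends and out of line with the month-12 endpoint

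*Protocol article*

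**What the plan says.** All references are to the protocol article.

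- **Quantitative process evaluation (Data analysis).** Routine output data are collected for the five intervention components, followed by a t-test "to compare intra-groups estimates to allow meaningful interpretations at the 6^th^ and 10^th^ month". These data are meant to show what was delivered and how far participants, professionals and lay health workers completed or adhered to the programme.
- **Qualitative process evaluation (same paragraph).** It runs in parallel. Two rounds of interviews "will be conducted at 6^th^ months (the completion of wait list control period) and 12^th^ month (project endpoint").
- **Outcome analysis (Data analysis).** For ordinal outcomes the model is to "compare groups at each follow-up (0^th^ month, 6^th^ month, and 12^th^ month"). Month 10 is mentioned nowhere else in the article.
- **Second cycle (Control group selection).** "On completion of the waiting period, the nurse and dietitian will invite the control group's participants for a face-to-face consultation". The section on intervention content sets telephone follow-up by the lay health worker at 6 months.
- **Table 2.** One indicator under financial subsidy is "Proportion of lay health workers that finished the 6-months follow-up". One under case management is "Number of biweekly reviews meeting conducted between lay health workers and nurse/ dietitian".
- **Lay health worker intervention content.** "Lay health worker will review case progress with nurse/dietitian once every 2–4 weeks".

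**The concern.** Two parts of one process evaluation, described as parallel, have different second time points, and the article gives no reason for the difference. The earlier one falls inside the second intervention cycle.

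An extract taken at month 10 sees the wait-list arm's programme when it is two thirds done. Indicators fixed early in a cycle, such as training sessions held or care plans drawn up, would lose little. Indicators that build up over the six months, or that can be read only at the end, would be incomplete for reasons unrelated to how well the programme was delivered. Completion and adherence are exactly what the process evaluation is asked to report, so for the second cycle the planned readout cannot give the answer.

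A separate and smaller mismatch concerns the review meetings between lay health workers and the nurse or dietitian. Table 2 labels them biweekly, while the intervention text allows a range of intervals.

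**Working it through.** The protocol states no figure to reproduce here. The check is of the timeline, plus simple arithmetic.

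**1. When the second cycle runs.** No single sentence gives its dates, so they are inferred:
- The randomization section separates the intervention slots by a 6-month wait.
- The control-group section brings wait-list participants in for consultation when that wait ends, so they start at about month 6.
- The intervention section gives a 6-month programme, so they end at about 6 + 6 = month 12.
- The interview schedule agrees: month 6 closes the waiting period and month 12 closes the project.

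**2. Share of the second cycle observed.**
- At month 10: (10 − 6)/6 = 4/6 = 67%.
- At month 12: (12 − 6)/6 = 6/6 = 100%.

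**3. Contacts possible by then.** One month is 52.18/12 = 4.35 weeks, so 4 months is 17.4 weeks and 6 months is 26.1 weeks. Calls and review meetings are both planned every 2 to 4 weeks. Expected contacts are weeks divided by interval.

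| Interval | By month 10 (17.4 weeks) | Full cycle (26.1 weeks) |
|---|---|---|
| 2 weeks | 8.7 | 13.0 |
| 4 weeks | 4.3 | 6.5 |

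On either interval, perfect delivery to month 10 yields 17.4/26.1 = 67% of a full cycle's contacts.

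**4. Which Table 2 indicators are affected.** Of 15 indicators, four clearly depend on elapsed time: completion of health goals, number of follow-ups, number of review meetings, and the share of workers finishing six months. For a cycle begun at month 6, the number of workers who have finished by month 10 is zero however well they worked.

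**5. Does a within-arm reading help?** The t-test is described as intra-group. The immediate arm's cycle is already over at month 6, so month 10 adds no further lay-worker contact for it. The wait-list arm has had none of its cycle at month 6 and 67% of it at month 10. On this reading too, month 10 does not capture a completed second cycle.

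**6. Biweekly against 2 to 4 weeks.** Taking biweekly as every two weeks, 26 weeks gives 26/2 = 13 meetings. The interval in the intervention text allows from 26/4 = 6.5 to 13. Table 2 states no target. If 13 were used as one (an assumption), a worker meeting every 4 weeks, within plan, would score 6.5/13 = 50%.

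**The case against.** The strongest reply is that month 10 appears once, against repeated use of months 6 and 12, and may simply be a slip for 12 in a secondary, descriptive evaluation. That may be so; the article does not say. It remains the only stated time for the second extract, and staff who follow it would draw the data too early.

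A reader might also infer more than the document supports:

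- **That poor apparent fidelity would distort the reading of the HbA1c result.** The arms are compared at month 6, while controls have had usual care only. The delivery that matters for that contrast is the first cycle's, which is fully observed by month 6.
- **That delivery will appear to fall by 33% between cycles.** This needs raw second-cycle counts at month 10 to be set against first-cycle totals at month 6. The article does not specify that comparison. If the totals are cumulative over the project, the month-10 figure cannot be below the month-6 one.
- **That the worker completion indicator will read 0%.** This holds only if it is calculated for the second cycle alone. Table 2 does not split it by cycle, and workers who finished the first cycle would count in a pooled figure.
- **That compliant workers will be scored as non-adherent.** Every two weeks is the frequent end of the permitted range, so the label does not fall outside the plan. It applies to one indicator, and no denominator is given.

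These limits stand. What they leave untouched is that a six-month cycle cannot be assessed for completion at its fourth month.

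**Conclusion.** The concern holds as an inconsistent and unsuitable time point for the second quantitative process readout. Followed as written, it observes 67% of the wait-list arm's cycle, cuts short about four of the 15 indicators for that cycle, and leaves its completion unassessable. This rests on the inferred start at month 6 and end at month 12, which the named project endpoint supports.

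It does not show that adherence as a whole will look falsely low. The 33%, 50% and 0% figures depend on comparisons or denominators that the article does not state. The first cycle and the month-6 comparison of HbA1c are not touched. The mismatch between biweekly and 2 to 4 weeks is real but minor. It would affect results only if the meeting count were judged against a target.

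**What to change.** - **Main change.** In the process-evaluation paragraph of Data analysis, move the second quantitative readout from month 10 to month 12, so that it coincides with the second interview round and the project endpoint and covers the whole second cycle.
- **Minor change.** Reconcile the review-meeting label in Table 2 with the interval in the intervention text. If the count is to be judged against a target, take that target from the schedule actually planned, which as now written allows 6.5 to 13 meetings over 26 weeks.

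**Cost.** A change of wording. The affected indicators come from administrative, clinical and service records already being kept, and month-12 activity is already planned. The drawback is that the second process readout arrives two months later.
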